## Abstract

**Background:**

High levels of emotional distress in cancer patients often goes unnoticed in daily clinical routine, resulting in severe undertreatment of mental health problems in this patient group. Screening tools can be used to increase case identification, however, screening alone does not necessarily translate into better mental health for the patient. Doctors play a key role in providing basic emotional support and transferring the patients in need of such specific support to mental health professionals. This study investigates whether a stepped care model, combining screening, doctor consultation and professional psycho-oncological service in a structured way, improves the emotional wellbeing of cancer patients.

**Methods/Design:**

This study is a cluster randomized trial with two parallel groups (intervention vs. care as usual), set in an academic hospital. Participants are cancer patients, a total of 1,000 at baseline. The intervention consists of stepped psychosocial care. Step one: screening for distress, step two: feedback of screening results to the doctor in charge of the patient and consultation with the patient, and step three: based on a shared patient-doctor decision, either transferal to the consultation liaison (CL) service or not. The outcome will be emotional well-being half a year after baseline, ascertained with the Hospital Anxiety and Depression Scale. Randomization will be done by the cluster randomization of wards.

**Discussion:**

Mental health problems not only cause emotional suffering but also direct and indirect costs. This calls for timely and adequate psychosocial support, especially as we know that such support is effective. However, not every cancer patient can and must be treated by a mental health professional. Allocating limited resources most sensibly and economically is of crucial importance for our healthcare system to ensure the best quality of care to as many patients as possible. It is the hope of the STEPPED CARE trial that this model is both effective and efficient, and that it can be implemented in other hospitals as well, if proven to be effective.

**Trial registration:**

Clinical Trials Register (Clinicaltrials.gov) identifier: NCT01859429 registration date 17 May 2013.

## Background

Psychosocial distress in cancer patients causes significant financial and emotional costs. It is associated with high utilization of health services, low quality of life and increased mortality [1, 2]. Meta-analyses show that one third of all cancer patients in acute clinics suffer from severe emotional distress and psychiatric comorbidity [3–5]. Unfortunately, such distress often goes undetected by healthcare providers, doctors and nurses alike [6–8]. This can result in considerable undertreatment of mental health problems [9]. Verdonck-de Leeuw *et al*. found in their prospective study that only 21% of highly distressed cancer patients were referred to a psycho-oncologist or a community worker [10]. We saw in one of our studies that only 9% of those cancer patients with a comorbid mental health condition were referred to a mental health specialist within three months of the diagnosis [11].

Such poor uptake of mental healthcare can only partly be explained by patients’ denial of emotional problems or hesitation to seek professional help. On the contrary, if patients are requested to indicate with whom they would like to speak about their emotional problems, one third of patients express the wish to consult a psycho-oncologist, and more than 80% request their physician [12].

It has been shown that if patients are asked to complete a short questionnaire to report psychosocial problems, under-diagnosis of poor mental health can be considerably decreased [7, 13, 14]. However, better identification of distressed patients does not necessarily translate into better patient care and, eventually, to improved mental health. For example, implementing screening for depression into the clinical routine did not improve mental health nor did it reduce supportive care needs in a clinical trial [15], at least not for the entire group of patients; only those with medium or high levels of distress benefited from the screening. Velikova *et al*. found in their three-arm trial (arm one: screening and feedback to the physician; arm two: screening only, no feedback and arm three: no screening) that completing a questionnaire was the crucial element for improving quality of life in cancer patients, whereas the feedback to the physician improved mental health [16].

It thus seems that patients’ mental health can be improved by a smart combination of routine screening and the involvement of healthcare professionals. It is the aim of the current study to test the effect of such a healthcare model.

### Aim and objectives

This study examines the effect of stepped psychosocial care (screening, consultation with a doctor and referral to psychosocial services) on mental health in cancer patients who are admitted for oncological treatment in a hospital.

The objectives are:to determine the feasibility of integrating a new strategy to detect and treat mental health problems of cancer patients in different clinics and wards (stepped care);to investigate the effect of this new strategy (stepped care) on patients’ mental health;to examine the medium-term (six-month) effects of the new strategy (stepped care).

The primary endpoint is patient-reported mental health. Secondary endpoints are social functioning, psychiatric comorbidity, satisfaction with care and utilization of healthcare.

## Methods/Design

### Design

Experience from previous studies teaches us that investigating complex behavioral interventions with ‘simple’ randomized trials can create misleading results. If, for example, students in a class are individually randomized to either be trained to stop smoking or not, the outcome ‘change in frequency of smoking’ will not entirely be related to the training itself. Students will talk to each other in the class, and, especially if one of the informal leaders (‘opinion maker’) in this class stops smoking, this will affect other students and they will be more likely to stop smoking as well. From a public health perspective, this is a most welcome effect. Technically speaking, however, this is an undesired effect, because it will blur the effects of the intervention; students in the control group will show an effect as well. In other words, individual randomization for the purpose of testing behavioral interventions in larger groups will likely result in an underestimation of the treatment effect. An alternative is the use of cluster randomization [17]. Here, clusters of individuals are randomized rather than individuals themselves, for example wards or clinics.

In our cluster randomized study, we randomized wards. Two parallel groups are compared and the intervention is expected to be superior to the control arm. The setting of this study is an academic hospital: University Medical Center Leipzig in Leipzig, Germany. Informed consent is obtained from each study participant after admittance to the ward, before the baseline assessment.

### Intervention arm (arm one)

The intervention is a stepped care model to provide targeted psychosocial help to cancer patients and consists of three steps.

Step one: each patient is screened for distress. The results of this screening are electronically computed, graphically visualized, and fed back to the clinician in charge. Patients’ level of distress is visualized by colors analogue to traffic lights: green = no or little distress, yellow = medium level of distress and red = high level of distress). The doctor can also view the detailed numeric results.

Step two: if the patient is at a medium or high level of distress, the doctor performs a brief interview along with their routine consultation with this patient. Together, they should discuss the psychosocial problems the patient currently has and decide on further steps. This second step is a key element in the stepped care model. It ensures the following: a) that the patients have access to the doctor to discuss their emotional problems, which is an important supportive care need for many patients [18], b) ‘false positives’ can be detected early, c) the clinician remains the key person for decisions on patient care and d) the patients can express their needs or concerns regarding psychosocial support. Studies show that this procedure is well accepted by patients and physicians [19, 20]. As doctors frequently feel insufficiently prepared to talk with patients about their emotional problems, and sometimes avoid such consultations, they are trained individually to perform this task. They learn how to, within the limited consultation time, ask questions, respond to patient concerns, consider their supportive care needs and provide further help.

Step three: if the patient and doctor decide that psychological support is needed, the hospital’s psycho-oncological consultation liaison (CL) service is informed and provides mental healthcare. If the patient has financial, vocational or other social problems, the hospital’s social service is called. If necessary, further support in the outpatient setting when the patient is discharged from the hospital is organized by these two teams.

Quality assurance: the team of this CL service consists of psychologists with formal training in psychotherapy, either cognitive-behavioral or psychodynamic. The social services team consists of professionally trained social workers. Both CL and social services provide support according to the current guidelines. The psychotherapists receive regular supervision by a fully trained senior psychotherapist. Adherence to the stepped care model is monitored by asking the patients whether their doctor has discussed emotionally relevant topics.

### Care as usual arm (arm two)

Patients who are treated on wards in the control arm receive care as usual. This means, doctors can call CL service and the hospital’s social service whenever they feel it is necessary. Doctors do not receive specific training to detect distress or to talk with the patients about emotional problems.

### Data collection

The primary endpoint mental health is ascertained with the Hospital Anxiety and Depression Scale (HADS) [21]. HADS identifies depressed patients with a sensitivity of 0.96 [22]. Social problems are measured with the European Organisation for Research and Treatment of Cancer Quality of Life Questionnaire Core Instrument (EORTC QLQ-C30), using the social functioning and role functioning scales [23]. Satisfaction with care is measured with the Quality of Care from the Patients Perspective questionnaire (QPP) [24], psychiatric comorbidity is measured with the Structured Clinical Interview (SCID) [25]), and the utilization of medical care is measured with the questionnaire used in the German Federal Health Survey [26]. Clinical data are obtained from the medical records. The provision of CL services and/or social services is ascertained from the hospital information system.

The patients are interviewed at the beginning (t1) and the end (t2) of the hospital stay, three months after baseline (t3) and six months after baseline (t4). At t1 and t2, data collection is done electronically with the help of tablet computers. At t3 and t4, it will be done via phone or face-to-face, depending on the patient’s preference. For patients who prefer paper-based data collection, this is possible as well. The equivalence of both methods is well documented [27, 28, 16]. The Computer-Based Health Evaluation System (CHES) software (Evaluation Software Development, Innsbruck, Austria) is employed for electronic data capture [29]. Electronic data capture ensures that no missing data are in the data set unless the patient quits the study. Study nurses with an academic psychology education contact the patients, inform them about the study, obtain written informed consent and perform data collection. Patients in the control wards undergo the same assessments as patients in the experimental wards.

### Eligibility

Patients aged 18 years or older of both sexes and with all types and stages of cancer are eligible for this study. They must be admitted to the University Medical Center Leipzig for diagnosis or treatment of cancer in one of the following departments: Urology, Pneumology, Maxillofacial Surgery, Radiation Oncology, Gynecology, Neurosurgery, Visceral Surgery, Orthopedics, Gastroenterology, or Laryngo-Rhino-Otology. Patient exclusion criteria are insufficient command of German and no written informed consent.

### Sample size

At the University Medical Center Leipzig, 2,000 patients with malignant diseases are treated per year according to the local cancer registry. Of those, about 350 are ineligible for the study because of age or because they are treated at a ward that is not participating in this study, leaving 1,650 eligible patients per year and 137 per month. Thus, about 1,200 patients can be approached initially. Assuming that 20% of patients will decline participation at t1, this leaves about 1,000 patients participating at baseline. Based on previous experience from a large epidemiological study with cancer patients at the University Medical Center Leipzig [22], we assumed that 20% of the patients would drop out during the follow-up period due to death or withdrawal from the study, leaving 800 patients at t4.

Cluster randomized trials must take into account the within- and between-cluster variation by increasing the sample size [30]. The between-cluster-variation coefficient could only be approximately estimated because of a lack of data in the literature. We therefore used the recommendation of Hayes and Bennett [30] and assumed k = 0.2. We further assumed an equal cluster size. In our trial, 13 clusters are included and randomized. The low number of clusters was considered in the sample size calculation with a specific formula (t-distribution). Data from a previous large study in the same hospital [22] suggests that the average HADS score in cancer patients is 13, with a standard deviation of 7. This is the expected mean HADS score in the control arm at t4. With 13 clusters, k = 0.2, α = 0.05, a power of 80%, and n = 400 per arm, a delta in HADS scores of 5.5 can be identified. If k should be k = 0.1, a difference of 4.1 can be detected.

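### The printed detectable differences (5.5 at k = 0.2, 4.1 at k = 0.1) do not follow from the stated between-cluster coefficient of variation; the same inputs give about 4.1–4.7 and 2.5–2.7

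*Protocol article*

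**What the plan says.** All the material is in the Sample size section of the protocol article. The clustering parameter is introduced with the remark that "The between-cluster-variation coefficient could only be approximately estimated because of a lack of data in the literature", and a value of 0.2 is then adopted on the recommendation of a cited methods paper (reference 30). No intracluster correlation is mentioned.

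The other inputs are printed. "In our trial, 13 clusters are included and randomized", and "We further assumed an equal cluster size". The small number of wards is handled by a t-based formula that is named but not shown: "The low number of clusters was considered in the sample size calculation with a specific formula (t-distribution"). An earlier study in the same hospital suggests that "the average HADS score in cancer patients is 13, with a standard deviation of 7", and this mean is expected in the control arm at t4. With α = 0.05, 80% power and 400 per arm, "a delta in HADS scores of 5.5 can be identified". The alternative follows: "If k should be k = 0.1, a difference of 4.1 can be detected".

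**The concern.** A between-cluster coefficient of variation is the between-ward SD divided by the mean. An intracluster correlation is the between-ward share of the total variance. The same number means different amounts of clustering on the two scales. The name given to k, and the fact that a mean of 13 is supplied at all, point to the coefficient of variation, yet the printed differences behave as if k were a correlation.

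This is the article's only power statement. If the differences are wrong for the stated k, readers get a wrong picture of what the design could show with 80% power. If instead the label is wrong, the citation offered for the clustering assumption does not support the value used, and anyone reusing k = 0.2 for a later ward-randomised trial would carry over the wrong quantity.

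**Working it through.** **Inputs from the Sample size section.** 13 wards, so 6.5 per arm on average; 800 patients at t4, so m = 800/13 = 61.54 per ward; mean 13; SD 7 (variance 49); α = 0.05; power 80%.

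**Assumed, because not stated.** Two-sided test; 13 − 2 = 11 degrees of freedom. The multiplier is t(0.975; 11) + t(0.80; 11) = 2.201 + 0.876 = 3.077 (squared, 9.465).

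**1. What reproduces the printed pair.** Treat k as an intracluster correlation ρ, with δ = 3.077 × √[2 × 49 × (1 + (m − 1)ρ)/400].
- ρ = 0.2: design effect 1 + 60.54 × 0.2 = 13.108; δ = 3.077 × √3.211 = 5.51.
- ρ = 0.1: design effect 7.054; δ = 3.077 × √1.728 = 4.04.
- With a 6 and 7 split of wards: 5.53 and about 4.06.

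**2. k as a coefficient of variation, between-ward SD the same in both arms.** δ = 3.077 × √[2 × ((13k)² + 49/m)/6.5], with 49/m = 0.796.
- k = 0.2: (2.6)² = 6.76; δ = 3.077 × √(2 × 7.556/6.5) = 3.077 × 1.525 = 4.69.
- k = 0.1: (1.3)² = 1.69; δ = 3.077 × √(2 × 2.486/6.5) = 3.077 × 0.875 = 2.69.
- Taking 7 as the total rather than the within-ward SD, or splitting the wards 6 and 7, moves these only within 4.66–4.70 and 2.68–2.70.

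**3. k as a coefficient of variation, between-ward SD proportional to each arm's mean.** For a reduction, solve 6.5δ² = 9.465 × [2 × 49/m + k²(13² + (13 − δ)²)].
- k = 0.2: δ = 4.10.
- k = 0.1: δ = 2.53.

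**4. Ratio of the two differences.** In step 2 the multiplier cancels, so α, sidedness, power and degrees of freedom play no part.
- Step 2: √(2.486/7.556) = 0.57.
- Step 3: 2.53/4.10 = 0.62.
- Step 1: √(7.054/13.108) = 0.73.
- Printed: 4.1/5.5 = 0.745; allowing for rounding, 4.05/5.55 = 0.73 to 4.15/5.45 = 0.76.

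**5. Power at the printed differences if k is a coefficient of variation (noncentral t, 11 df).** About 91% (step 2) to 97% (step 3) for 5.5 at k = 0.2, and about 99% or more for 4.1 at k = 0.1.

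**6. The two scales compared.** k = 0.2 corresponds to an intracluster correlation of 6.76/49 = 0.14 if 7 is the total SD, or 6.76/(6.76 + 49) = 0.12 if it is the within-ward SD; k = 0.1 corresponds to about 0.03 either way. Conversely, with 7 as the total SD, correlations of 0.2 and 0.1 correspond to k = √(0.2 × 49)/13 = 0.24 and √(0.1 × 49)/13 = 0.17.

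**The case against.** The strongest defence is that the formula used is not shown, and some readings bring 5.5 within reach.
- If the between-ward SD scales with a mean that rises, k = 0.2 gives about 5.7. But k = 0.1 then gives 2.9, and the Design section expects the intervention to be superior.
- Randomisation was stratified, which might cost degrees of freedom. With 5 degrees of freedom, 6 wards per arm and constant between-ward SD, k = 0.2 gives 5.54, but k = 0.1 gives 3.18.

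So 5.5 taken alone is not wrong under every conceivable reading. Neither variant comes near 4.1 at k = 0.1, and neither rescues the pair.

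A reader might infer that k was certainly used as an intracluster correlation. The article does not establish that. It names k without printing its formula. With 6.5 wards per arm, the correlation reading gives 4.04, which rounds to 4.0; reaching 4.1 needs a 6 and 7 split that is nowhere stated. Reading k as a ratio of between- to within-ward variance fits about as closely (roughly 5.55 and 4.07).

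A reader might also infer that differences below 4.1–5.5 could not be detected, or that the sample size must change. Neither follows. The figures are differences detectable with 80% power, and smaller ones are detectable with lower power; a null result is better judged from its confidence interval. The sample rests on how many patients could be approached and retained, and the detectable difference was then read off that number. For a reduction in HADS the error is conservative.

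**Conclusion.** The point holds as an internal inconsistency between the stated k and the two printed differences. For a reduction in HADS, 5.5 exceeds the derived 4.1–4.7 by 0.8–1.4 points, and 4.1 exceeds the derived 2.5–2.7 by 1.4–1.6 points, so the second figure is at least 50% too large (4.1/2.7 = 1.52). In SD units the printed range is 0.59–0.79 (4.1/7 to 5.5/7); the derived values run from 0.36 to 0.67 (2.5/7 to 4.7/7).

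The exact figures rest on a two-sided test and 11 degrees of freedom, neither of which is printed. The mismatch at k = 0.1 and the mismatch in the ratio survived every variant tried that kept the stated inputs. Confusion with an intracluster correlation is the likely cause but remains unproven. Severity: should be fixed. The statement understates sensitivity under the plan's own k, promises no power that k would deny, and leaves enrolment as it is.

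**What to change.** State explicitly which quantity k is, then take one of two routes.
- If it is the between-ward coefficient of variation, recompute and restate both differences. Expect about 4.1–4.7 at k = 0.2 and 2.5–2.7 at k = 0.1. Say whether the between-ward SD is held constant or scales with the arm mean, whether 7 is the total or the within-ward SD, and which sidedness, degrees of freedom and ward split were used.
- If an intracluster correlation of 0.2 (alternative 0.1) was meant, relabel it, remove the attribution to the recommendation for k, and give the basis for the chosen values. The printed differences can then stand, subject to stating the ward split behind 4.1.

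The cost is a short recalculation and a rewording of one paragraph, with no change to the number of wards or patients.

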### Measures to reduce confounding and bias

Potential confounding will be controlled by randomization. Randomization was completed externally by the Center for Clinical Trials at University Medical Center Leipzig, Germany. In order to reduce baseline differences, the randomization was stratified according to the average frequency of psycho-oncological CL services in the past two years per department. This information was taken from the yearly documentation of the CL service.

By using standardized tools and training interviewers, a potential information bias will be reduced. Moreover, the study nurses collect data either always on intervention wards or always on control wards; they do not change trial arms. The patients are not told to which group they have been randomized. However, the intervention itself (screening, consultation with the doctor and referral to the CL service) obviously cannot be blinded. The results of the randomization can also not be concealed to the doctors because they have to change their consultation behavior in the intervention arm.

Selection bias is intended to be kept to a minimum through high participation rates. Based on previous experience [31], we know that highly distressed patients decline participation disproportionately more often. We control this effect by documenting the reasons for decline and then comparing participants and non-participants.

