### Statistical analysis

The main analysis will compare HADS scores of all patients at t4 in arm one versus arm two using t-tests. Subsequently, only patients highly distressed at baseline in the two groups will be compared regarding their HADS score at t4. Because of the limited number of departments, complete control for confounding cannot be guaranteed despite randomization; therefore the following variables will be subsequently adjusted for in a mixed-model analysis: sex, age, stage of disease and baseline distress. The analyses will be done as according to the intention to treat principle. No interim analyses are planned.

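### Ward randomisation was stratified by past CL-service frequency, but the named analyses omit that factor, so a ward-aware analysis would report too large a standard error if the factor predicts HADS

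*Protocol article*

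**What the plan says.** Design gives the unit of allocation: "In our cluster randomized study, we randomized wards". Sample size gives the number: "In our trial, 13 clusters are included and randomized". Measures to reduce confounding and bias says that "the randomization was stratified according to the average frequency of psycho-oncological CL services in the past two years per department", with the aim of reducing baseline differences.

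Statistical analysis fixes two steps. First: "The main analysis will compare HADS scores of all patients at t4 in arm one versus arm two using t-tests". Then, because the small number of departments may leave residual confounding, "the following variables will be subsequently adjusted for in a mixed-model analysis: sex, age, stage of disease and baseline distress".

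CL-service frequency is in neither step. The article does not give the number of strata, the relation between CL frequency and HADS, or the random effects of the mixed model.

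**The concern.** Stratified allocation removes most of the between-stratum variation from the arm difference. An analysis without the stratum still counts that variation as ward-level error. The estimate is then more precise than its standard error says, the test runs below its nominal level, and power is given away.

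This matters more than usual here, because with 13 wards precision depends almost wholly on between-ward variance. The omission also sits oddly with the stated reason for adjusting. The covariates are listed because randomising few units may not control confounding, yet the one variable thought important enough to constrain the randomisation is not among them.

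**Working it through.** **Inputs from Sample size.** 13 wards; 800 patients at t4, so 800/13 = 61.54 per ward; SD 7; control mean 13; α = 0.05; power 80%; k = 0.2, or alternatively 0.1. The between-ward SD is 0.2 × 13 = 2.6 (variance 6.76), or 0.1 × 13 = 1.3 (variance 1.69).

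**Assumptions.** Two-sided test; 7 versus 6 wards; equal ward sizes; two strata of 6 and 7 wards; the same between-ward SD in both arms; and f, the share of between-ward variance that the stratum explains. The article gives no value for f.

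**The plan's own figures.** The article states detectable differences of 5.5 (k = 0.2) and 4.1 (k = 0.1). The usual cluster formula is δ² = (q_α + q_β)² [2·SD²/m + k²(μ0² + μ1²)]/c, with c = 6.5 wards per arm and m patients per ward. At k = 0.2 it gives 3.8 (normal quantiles), 4.1 (t, 11 df) or 4.4 (t, one cluster added). At k = 0.1 it gives 2.3, 2.5 or 2.7. No variant tried gave both stated figures. That is a separate matter; the comparison below needs only the inputs.

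**Step 1: no stratum effect (f = 0), k = 0.2.** The sampling variance of a ward mean is 49/61.54 = 0.80, against a between-ward variance of 6.76, which is about 8.5 times as large.
- SE = √[(0.796 + 6.76)(1/6 + 1/7)] = √2.339 = 1.53.
- Without the stratum (11 df) the t quantiles sum to 3.077, giving about 4.7.
- With it (10 df) they sum to 3.107, giving 4.75. The ratio 3.107/3.077 = 1.01 is the price of a useless term.

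**Step 2: stratum in the model.** SE = √[(0.796 + (1 − f)·6.76)(1/6 + 1/7)], times 3.107:
- f = 0.10: 1.459 × 3.107 = 4.53
- f = 0.25: 1.347 × 3.107 = 4.19
- f = 0.50: 1.137 × 3.107 = 3.53 (3.55 by simulation)

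**Step 3: stratum left out.** The right comparator is not a fixed 4.7, because the unadjusted estimate also gains from the stratified allocation. Only its reported standard error fails to follow. At f = 0.50 the mean reported SE is 1.56 against a true 1.14. Simulation of a ward-level test gives:

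| k | f | Type I error, without / with stratum | Detectable difference, without / with stratum |
|---|---|---|---|
| 0.2 | 0 | 0.050 / 0.050 | 4.69 / 4.75 |
| 0.2 | 0.10 | 0.040 / 0.048 | 4.54 / 4.53 |
| 0.2 | 0.25 | 0.027 / 0.049 | 4.44 / 4.19 |
| 0.2 | 0.50 | 0.010 / 0.048 | 4.26 / 3.55 |
| 0.1 | 0.50 | 0.018 / 0.050 | 2.50 / 2.22 |

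**Step 4: the odd ward.** Thirteen wards cannot be balanced exactly. With splits of 3/3 and 4/3, the arms differ by 4/7 − 3/6 = 0.071 in stratum share. At f = 0.50 and k = 0.2 the strata differ by √[3.38/((6/13)(7/13))] = 3.69 points, so the unadjusted estimate shifts by 0.071 × 3.69 = 0.26. The table takes this shift in the direction that helps the unadjusted test. In the other direction, 4.26 becomes about 4.26 + 2 × 0.26 = 4.78. The gains shown are therefore at the low end.

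**Step 5: a t-test on patients.** If the main t-test is run on individual patients, its mean SE is about 0.52 at k = 0.2 against a true 1.52 (f = 0) or 1.14 (f = 0.50), with type I error of about 0.50 and 0.38. Ignored clustering dominates there, and the error is in the opposite direction.

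**The case against.** **The article is condensed, and stratum terms are often left to the SAP.** This is fair as far as it goes: even the random effects are not given. But the article does name its adjustment variables as a definite list, and the stratification factor is not on it. That is a choice stated in the document, not a detail passed over.

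**Nothing shows that CL frequency predicts HADS.** This stands. It measures service use, and the article says only that stratifying on it should reduce baseline differences. Baseline distress, already in the mixed model, may absorb part of any effect, and the further gain in that model was not computed. If f is zero, there is no gain.

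**The trial has power to spare at its own target.** At a difference of 5.5 with k = 0.2, simulated power of the ward-level test is about 0.90 without the stratum, and 0.95 (f = 0.25) or 0.99 (f = 0.50) with it. At k = 0.1 and 4.1 it is at least 0.98 either way. This limits the consequence for the planned difference, though not for smaller ones, and a test at 0.01 to 0.04 instead of 0.05 still misstates the evidence.

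**Stronger readings that do not hold.** A reader might infer that the balance from stratification is lost. It is not: apart from the odd ward, it stays in the estimate. A reader might also infer that the main analysis as worded has too wide a standard error. Its wording suggests a patient-level t-test, whose standard error would be too small.

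**Conclusion.** The point holds in a limited form. The analyses named in the article do not reflect the stratified randomisation. In a ward-aware analysis (the mixed model with a ward effect, or a ward-level test) the reported standard error is too wide to the extent that CL frequency predicts HADS at t4.

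Under the assumptions above and k = 0.2, adding the stratum changes the detectable difference hardly at all at 10% explained, by about 6% at 25% (0.25/4.44) and by about 17% at 50% (0.71/4.26). At k = 0.1 and 50% the gain is about 11% (0.28/2.50). The share explained is unknown, so the size is a range and not an estimate. The case for acting is the asymmetry: a loss of about 1% if the factor is irrelevant, against a correctly sized test and possibly a material gain if it is not.

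**What to change.** Add the CL-frequency stratum used in the randomisation as a fixed effect in the planned mixed model, with a ward effect, and in whatever cluster-aware analysis serves as the main comparison. If the strata are many or sparse, use the department's past CL frequency as one linear term instead; the measure is recorded per department, so wards of one department share a value. State the number of strata.

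The cost is one of 11 degrees of freedom with two strata or a linear term (two of 11 with three strata). No new data are needed, since the frequencies come from the CL service's yearly documentation. The change complements an analysis that respects clustering and does not replace one.
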